### Data safety and monitoring

Data monitoring and interim analyses will be done by the data safety and monitoring committee. The trial data safety and adverse effect monitoring committee (DSMC) will be established to monitor the adverse effects of the intervention on patients. The committee will be formed from TB expertise, academia, stakeholders, planners, and officials. Adverse risks or harms will not be possible because the intervention will not directly involve any invasive procedures or will not administer drugs that affect the study participants. The DSMC will be used as the protocol for data reporting and interim analyses that minimize bias. Then, the committee will give recommendations based on their findings, either continuing the trial as planned or stopping early for hazards, or stopping the intervention because continuing the intervention is futile for the patient and community [32–35]. The committee will meet once a month and give feedback based on their assessment findings. The committee will recommend discontinuing the intervention when the intervention brings a negative impact on the health, social, cultural, spiritual, privacy, and violation of patient confidentiality. An interim analysis will be used to evaluate the data from an ongoing trial and address the primary research question and modify the intervention. A trial steering committee (TSC) will be formed from Bahir Dar University College of Medicine and health sciences ethics review board members and post-graduate office. The responsibilities of the TSC will be used to approve the main study protocol and any amendments, monitor and supervise the trial toward its interim analysis, and resolve problems brought by the trial coordinating team.

### Trial adherence and retention strategies

Adherence of the participants in both the intervention and control groups will be assessed using participants’ self-reports and direct observation by trained field supervisors. Regular communication and feedback will be made between the supervisors and the traditional care providers and healthcare workers. The project manager will be regularly communicated with supervisors, traditional care providers, and TB focal persons to minimize the attrition rate of participants in the intervention and control arms. Those participants who discontinue and completed the follow-up from the intervention and the number of outcomes that occurred during follow-up will be reported in the final dissertation.

### Patient public involvement

During the development of this research project, formative consultation occurred with the community advisory group and stakeholders including, Amhara Public Health Institute, local TB control program leaders, TB patients, traditional healers, and faith leaders through face-to-face interviews and focus group discussions, as part of our previous qualitative study [36]. The community and consumer representatives will be involved at each stage of the research project, including the planning, implementation, follow-up, and dissemination of research findings.

### Control groups

The control sites will follow the existing passive case-finding system (self-referral patients to nearby health facilities that use the same national guidelines to treat TB). The findings obtained from the control groups will be compared with those obtained from the intervention groups. Finally, changes between the two groups will be assessed and concluded.

### Trial status

Unique Protocol ID: 353/2021.

ClinicalTrials.gov ID: NCT05236452.

The date recruitment began: July 1, 2022.

Registration date: July 22, 2022.

Approximate date when recruitment will be completed: December 30, 2023 [anticipated].

### Outcomes of interest

The study will have three outcomes of interest. The primary outcome is the TB case detection rate. The secondary outcomes of interests are diagnosis delay and costs of TB care. The case detection rate will be expressed as percentage. The diagnosis delay will be defined as the time interval between the onset of symptoms and the confirmation of TB diagnosis, which includes patient delay and health system delay. The cost of TB care will include both direct and indirect costs of the patient for TB care and treatment as collected from the patients themselves and their medical records. Direct costs include out-of-pocket payments for medical services (counseling, drugs, laboratory tests, X-rays, and hospital stays) and non-medical services such as transportation, food, and accommodation costs.

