Delays in the diagnosis and treatment of TB lead to slow progression of the disease, poor treatment outcomes, and an increased risk of TB transmission [18]. Delayed TB diagnosis can result in physical, social, and mental health problems such as depression, anxiety, and psychosis [19]. It can also affect social life and impose an economic burden on TB-affected families [20–22]. TB diagnosis delay in Ethiopia is unacceptable, with a previous study showing that 91% of TB patients exceeded 31 days in total delay [23]. Delays in TB diagnosis were also high in the Amhara region, with three-fifths of patients having delays in TB diagnosis and treatment [24]. The lack of appropriate intervention was the main contributor to the delay in TB diagnosis [25].

Since more people first visit traditional care, they delay visiting the modern healthcare system. Studies show that the first visit to traditional healers can lead to lower case detection, longer diagnostic delays, and higher costs. A study conducted by the WHO showed that 70–80% of the population in developing countries uses traditional medicine [26]. Traditional medicine encompasses knowledge and practices that are inherent to various cultures, whether or not they can be rationalized, and that are used to maintain health as well as to prevent, diagnose, treat, and improve physical and mental illness [27].

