### Definition of terms

Important variables are defined according to the researchers’ operation used in the research and all definitions are annexed in Appendix 2.

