### Sample size determination

#### Sample size for TB diagnosis delay among tuberculosis patients

To estimate the effect of integrating traditional care with modern care on diagnosis delay, the sample size will be calculated using the two-sample comparison of proportions formula in STATA version 16. A chi-squared test with two independent samples will be used to calculate the sample size using diagnosis delay. By considering the previous study conducted in the Amhara region with the proportion of diagnosis delay P1 = 59.9% [24] and by assuming that the effect of the intervention on diagnosis delay decreased by 14% in the intervention group as compared to the control, P2 = 45.9%. By considering the probability of a type 1 error of 0.05, 95% CI, power of 80%, and a 10% non-response rate, the total sample size will be 438. Since the study is a multicenter, individually randomized trial, the design effect will be used. According to the multicenter design effect formula, the design effect formula, the $$\mathrm{design\ effect}=\frac{\upsigma {e}^{2}}{\sigma {e}^{2}+\sigma {B}^{2}}$$ = 1 − *ρ*. The majority of formulas applied to multicenter designs have a better relative accuracy (ICC less than 0.052) for designs including more than 10 centers. Assuming that randomized will be balanced and stratified on centers that have equal group sizes [37], assuming the variation between the centers will be 0.05, the design effect = 1 – *ρ* = 0.95. Therefore, the final sample size is calculated as sample size * design effect; 438 * 0.95 = 416 (208 for each arm).

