### Data analysis

Descriptive statistics will be used to summarize the baseline data. A chi-square test will be performed to compare the baseline characteristics of the intervention and control groups. Comparisons of detection rate, diagnosis delay, and costs of TB care between and within the intervention and control groups will be done using independent samples and paired sample *t*-tests, respectively. The independent *t*-test will be also used for the knowledge and attitude of post-test results of practitioners.

Logistic regression analysis will be used to determine the factors associated with case detection rate and diagnosis delay. A univariable logistic regression model will be fitted, and variables having a *p*-value less than 0.25 in the univariable logistic regression model will be fitted into the multivariable models. Variables with a *p*-value < 0.05 in the multivariable logistic regression model can be considered statistically significant. Crude and adjusted odds ratio (OR) with 95% confidence interval (CI) will be calculated to measure the strength of association between the dependent and independent variables. The fitness of the logistic regression model will be checked using the Hosmer–Lemeshow goodness of fitness test at *p*-value > 0.05. Multicollinearity between explanatory variables will be checked by a variance inflation factor (VIF), and variables with a VIF > 5 will be excluded from the final models.

Generalized linear mixed models (GLMM) will be used to assess the impact of the intervention on the change of cost of TB care. This GLM enables us to accommodate the correlation of observations due to the pre and post-intervention measurements and clustering of individuals within randomly selected clusters. Model fitting will be checked before the analysis is done. The effects of potential confounding factors will be controlled. The variance of the cluster-level residual errors will be computed using the intercept-only model. The variation between and within the groups will be analyzed.

Subgroup analysis will be employed to explore whether there is evidence that the detection variation depends on certain patients or facility characteristics. Covariate adjusted analysis will also employ to refine the analysis of case detection variation in the intervention and control arms the fact that some baseline characteristics may be related to outcome and unbalanced between the groups.

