### Definition of terms

Acceptability: Acceptability refers to the agreement of practitioners and other stakeholders on the appropriateness, suitability, adequacy, or effectiveness of the intervention.

Active case findings: Active case finding intervention consisting of community-based approaches (TB screening outreaches, community outreach/house-to-house screening, and contact tracing of members of households of TB patients) and systematic screening of target groups (pregnant women, women attending maternal and child health clinics, outpatient department, and HIV-infected individuals).

Catastrophic costs: Total costs (indirect and direct combined) incurred during illness and treatment exceeding a given threshold (20%) of the household’s annual income. Total direct and indirect costs incurred from the onset of symptoms to the end of TB treatment will be considered the numerator, as well as annual household income, will be considered the denominator [46].

Case detection: Case detection is defined as TB being diagnosed in a patient and is reported within the national surveillance system and then to WHO.

Case detection rate: The case detection rate is calculated as the number of cases notified divided by the number of cases estimated for that year, expressed as a percentage [41].

Case notification: Notification is the process of reporting diagnosed TB cases to WHO; the data collected by this process.

Diagnostic delay: Time interval between the onset of symptoms and labeling of the patient as a patient with TB (TB diagnosis).

Feasibility: An umbrella term used to describe any type of study relating to the preparation for the main study. A feasibility study is an analysis that takes all of a project’s relevant factors into account including economic, technical, legal, and scheduling considerations to ascertain the likelihood of completing the project successfully [47].

Health care system delay: Health system delay is the time interval between the date of health-seeking behavior at a health care provider and the initiation of anti-TB treatment.

Holy water: Holy water is water that has been blessed by a member of the clergy and used in baptism to heal individuals of their physical, psychological, and spiritual illnesses.

Patient delay: Patient delay is the time interval between the onset of symptoms and presentation to a health care provider.

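### Diagnosis delay is defined as a time interval, sized as a proportion delayed with no cut-off in days, and compared between arms by a t-test, so the stated 80% power belongs to an undefined event and to a test that is not the planned one

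*Protocol article*

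**What the plan says.** Four places in the protocol article treat the same secondary outcome on different scales.

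- **Outcomes of interest:** "The diagnosis delay will be defined as the time interval between the onset of symptoms and the confirmation of TB diagnosis". This is a number of days. Appendix 2 (Definition of terms) also defines diagnostic delay as an interval. Neither gives a threshold.
- **Sample size for TB diagnosis delay:** "the sample size will be calculated using the two-sample comparison of proportions formula in STATA version 16", "with the proportion of diagnosis delay P1 = 59.9"%, against 45.9% with the intervention, and a chi-squared test. Here delay is a yes/no event.
- **Data analysis, first paragraph:** "Comparisons of detection rate, diagnosis delay, and costs of TB care between and within the intervention and control groups" are to be made by independent-samples and paired t-tests respectively. The between-arm test of delay is therefore a difference in means.
- **Data analysis, second paragraph:** "Logistic regression analysis will be used to determine the factors associated with case detection rate and diagnosis delay", with odds ratios. Delay is binary again, in a model of associated factors.

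On where a threshold should be found, the Definition of terms section says that "all definitions are annexed in Appendix 2". Appendix 2 has entries for diagnostic, patient, health care system, treatment and total delay. None of them states a number of days beyond which a patient counts as delayed.

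**The concern.** A difference in mean days and a difference in the proportion beyond a cut-off are different estimands. They have different power and need not agree. The article justifies its numbers with the second and plans to test the first. The second also cannot be computed as it stands, because the event has no definition.

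Two things are at stake. First, the 80% power does not describe the planned between-arm analysis. Second, if both a proportion and a mean are reported with neither named as the analysed endpoint, the objective on delay has two chances of a nominally significant result.

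**Working it through.** **Inputs.** From the sample size section: P1 = 0.599, P2 = 0.459, type I error 0.05 (two-sided reproduces the plan's figure), power 80%, 10% non-response, multiplier 0.95, 208 per arm. Assumed here, because the article gives no distribution: delays are log-normal, the intervention shifts log days by a constant, and the log-scale SD lies between 0.8 and 1.3. Clustering is ignored throughout, so every figure is nominal.

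**1. The plan's own figure.** With pooled p = (0.599 + 0.459)/2 = 0.529:

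n per arm = [1.960·√(2·0.529·0.471) + 0.842·√(0.599·0.401 + 0.459·0.541)]² / 0.14² = (1.3836 + 0.5882)² / 0.0196 = 198.4, so 199 per arm and 398 in total.

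398 × 1.10 = 437.8, so 438. Then 438 × 0.95 = 416.1, so 416, or 208 per arm. Both stated figures reproduce, so the sizing rests wholly on the yes/no version of delay. Whether 0.95 is a proper multiplier is a separate question.

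**2. The planned effect as a shift.** z(0.599) − z(0.459) = 0.251 − (−0.103) = 0.354 SD of log days.

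**3. Power for that one effect at 208 per arm, two-sided 5%.**

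| Analysis | Calculation | Nominal power |
|---|---|---|
| Proportion delayed, as sized | Φ[(0.14·√208 − 1.3836)/0.699] = Φ(0.909) | 82% |
| t-test on log days | Φ[0.354·√(208/2) − 1.960] = Φ(1.647) | 95% |
| t-test on raw days, log-SD 0.8 | simulation | about 86% |
| t-test on raw days, log-SD 1.0 | simulation | about 80% |
| t-test on raw days, log-SD 1.3 | simulation | about 67–68% |

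The planned t-test can thus fall above or below the 82% of the sized comparison, depending on a skewness that the article does not discuss.

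**4. Two scales, no true effect.** Simulating identical log-normal arms of 208, and counting a trial as positive if either the chi-squared test at one cut-off (59.9% beyond it) or the raw-days t-test gives p < 0.05, the chance of at least one positive is about 9% for log-SDs from 0.8 to 1.3.

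**5. Does the cut-off alone overturn the sample size?** Applying the 0.354 SD shift at other cut-offs, with 208 per arm:

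| Control proportion delayed | Intervention proportion | Nominal power |
|---|---|---|
| 75% | 62.6% | 78% |
| 59.9% | 45.9% | 82% |
| 50% | 36.2% | 81% |
| 40% | 27.2% | 79% |

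Under a constant shift it does not, over this range. The cut-off is needed to define the event, more than to rescue the sample size.

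**The case against.** - **Is the logistic regression a rival test of the intervention?** A reader might infer that delay is tested twice between arms. The text does not say so: it gives the logistic model the task of finding associated factors, with variables screened at p < 0.25, and gives the between-arm comparison to the t-test. This part of the objection stands. The conflict remains without it, because a chi-squared comparison of proportions was sized and a t-test is planned.
- **Does the abstract settle the method?** It says generalized linear mixed models will compare the outcome of interest between arms. The Data analysis section names that model only for the cost of TB care, and the abstract does not say on which scale delay would enter.
- **Is the threshold simply left to a fuller document?** An analysis plan not shown here may fix it, so one cannot conclude that the cut-off will be chosen after seeing the data. But this article itself sends the reader to Appendix 2 for all definitions, and its printed scales conflict whatever another document says.
- **Could 31 days be the cut-off?** The Background reports that "91% of TB patients exceeded 31 days in total delay". That is total delay, which Appendix 2 runs to the start of treatment, so it is a different interval. It is not adopted as the trial's threshold and cannot serve to show what power the trial would have.
- **Is the error rate worse than 9%?** Searching over several cut-offs would raise it, but the article lists no set of cut-offs to search.
- **Is skewness already handled?** The Data processing and management section checks numeric data for normality. It does not say what happens to the t-test if the check fails.
- **Is a binary endpoint wrong in itself?** No. A proportion delayed is a legitimate choice, provided it is defined and is the one tested.

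**Conclusion.** The point holds as an inconsistency of scale plus a missing definition. The 80% power for diagnosis delay applies to a yes/no event that the article does not define and to a test that its analysis section does not plan. On the assumptions above, the same effect carries nominal power of 82% as sized, about 67–86% by the planned t-test if it is run on raw days, and 95% on log days. Reporting both scales gives about a 9% false-positive chance.

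These figures illustrate how far the endpoints differ. They are not estimates of this trial's power: with six districts randomised, clustering changes both the power and the error rates, and the gaps between analyses need not stay the same. Delay is a secondary outcome, so the primary conclusion on case detection is untouched. The change should be made, but it does not put the trial in doubt.

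**What to change.** Name one analysed scale for the between-arm comparison of delay, and use it consistently in Outcomes of interest, the sample size section and Data analysis. Test it in a model that accounts for clustering by district. Either choice is sound:

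1. Log days as the analysed endpoint, reported as a ratio of geometric mean delays, with the proportion delayed as supportive.
2. The proportion delayed as the analysed endpoint, as sized.

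Under both:

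- State in Appendix 2 the single cut-off in days that makes a patient delayed, the same as the one behind the 59.9%. The sponsor must take it from the cited study, since the article does not print it.
- Replace the raw-days t-test as the between-arm test.
- Say in the sample size section which endpoint the 80% power refers to. Under option 1 that is the supportive proportion.

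The cost is wording only. The dates of symptom onset and diagnosis are already needed for the defined interval, so no new data are required. The small downside of option 1 is that a ratio of delays is less familiar to readers than a percentage; the supportive proportion covers this.

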### Measurements

The case detection rate will be calculated as the number of cases notified divided by the number of cases estimated for that year, expressed as a percentage [41]. The WHO estimator for the year 2022 was 132 per 100,000. Estimating the number of TB cases for that year will be computed by using that year/100,100 * total population of the catchment area. Estimating the number of TB cases for that year will be computed by using total cases in the year/100,100 * total population found in the catchment area multiplied by 100, expressed as a percentage.

Patient costs and their annual incomes collected in Ethiopian birr will be converted to US dollars ($) with an average exchange rate for the dates during which data collection took place. The total costs will be considered the sum of the entire direct and indirect costs of TB illness to patients. Out-of-pocket payment for health care (medical) will be the direct payment made for medical care directly by individuals at the time of service using minus insurance reimbursement. Out-of-pocket costs will be a payment for formal medical services, informal traditional practitioners, clinics, health centers, pharmacies, and hospitals for medical services and products such as diagnosis, treatment, and medicine. Out-of-pocket payment net will be a total out-of-pocket payment (medical and non-medical) minus any reimbursement received for payments made. The direct costs will be calculated by the sum of any payment affected by medical and non-medical costs. The medical costs will be the sum of out-of-pocket payments for TB diagnosis and treatment made by TB patients in a given household buying medicines, payments for diagnostic tests, and net reimbursements. The direct non-medical costs were out-of-pocket payments for transport, accommodation, and food before and during TB diagnosis. An indirect cost is costs incurred as a result of TB healthcare seeking and hospitalization, during the TB episode. The total period of absence (in hours) will be multiplied by the hourly wage rate of the absent worker.

Catastrophic costs due to TB: total costs (indirect and direct combined) exceeding a given threshold of the household’s annual income, here defined as exceeding 20%, as recommended by WHO [42].

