### Project timeline

The timeline of enrollment, interventions, and assessments of the project is well set. The enrollment started in July 2022, and the project will be closed in January 2024. The detailed schedule is annexed in Appendix 3.

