TB suspect: Any person who presents with symptoms or signs suggestive of TB. The most common symptom of pulmonary TB is a productive cough lasting more than 2 weeks, which may be accompanied by other respiratory symptoms (shortness of breath, chest pains, hemoptysis), and/or constitutional symptoms (loss of appetite, weight loss, fever, night sweats, and fatigue) [48].

Traditional healer: The term traditional healer refers to those practitioners who provide any health and health-related healing services using their indigenous knowledge, and who are registered with legitimate authorities, while religious healers refer to religious leaders who provide healing services at holy water sites [49].

Traditional medicine: TM is the total of the knowledge, skills, and practices based on the theories, beliefs, and experiences indigenous to different cultures, whether explicable or not, used in the maintenance of health as well as the prevention, diagnosis, improvement, or treatment of physical and mental illness [27].

Total delay: The total delay is the time interval from the onset of illness until the initiation of anti-TB drugs. It is the sum of two-time intervals: the diagnostic delay and the treatment delay. The total delay is also the sum of patient and healthcare system delays.

Treatment delay: Time interval between the TB diagnosis and the initiation of anti-TB drugs.

## Appendix 4

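### Secondary outcomes need reconciling: one cost component stops at diagnosis while catastrophic cost runs to end of treatment, the powered catastrophic-cost proportion has no named test, and diagnosis delay is described by components that sum to total delay

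*Protocol article*

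**What the plan says.** **Delay.** Outcomes of interest defines diagnosis delay as "the time interval between the onset of symptoms and the confirmation of TB diagnosis, which includes patient delay and health system delay". Appendix 2 (Definition of terms) also ends diagnostic delay at diagnosis. Its entry for the second component reads: "Health system delay is the time interval between the date of health-seeking behavior at a health care provider and the initiation of anti-TB treatment". It then adds: "The total delay is also the sum of patient and healthcare system delays". Total delay itself ends when anti-TB drugs start, and treatment delay (diagnosis to drugs) is listed as a separate interval.

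**Cost window.** For catastrophic cost, Appendix 2 states: "Total direct and indirect costs incurred from the onset of symptoms to the end of TB treatment will be considered the numerator". Measurements states: "The direct non-medical costs were out-of-pocket payments for transport, accommodation, and food before and during TB diagnosis". In the same section, medical costs cover both diagnosis and treatment, and indirect costs cover the TB episode. The sum is compared with 20% of annual household income.

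**Cost endpoint.** The Abstract and Study design and participants name catastrophic costs as an outcome. Outcomes of interest names the cost of TB care. The cost sample size uses a chi-squared comparison of the proportion with catastrophic cost, 40% versus 27%. Data analysis lists independent and paired t-tests on costs, a generalized linear mixed model (GLMM) on change of cost, and logistic regression for case detection rate and diagnosis delay only.

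**Dates.** Randomization and recruitment gives recruitment from 1 July to 30 September 2022. Trial status gives 1 July 2022 to an anticipated 30 December 2023. Project timeline says: "The enrollment started in July 2022, and the project will be closed in January 2024".

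**The concern.** Both secondary outcomes depend on dates and components that field staff must record the same way for every patient. An assessor who follows the component wording for delay, or the Measurements wording for non-medical cost, will record a different quantity from one who follows Appendix 2.

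For cost, the component left out feeds a yes/no threshold, so the omission changes how households are classified and not only the size of a mean. The proportion that fixed the number of patients is also not the quantity for which Data analysis names a test. The trial could therefore report a cost result on a scale for which no detectable difference was ever set.

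**Working it through.** **1. Delay.** Let O be symptom onset, S presentation to a provider, D diagnosis and T the start of anti-TB drugs.

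- Diagnosis delay (Outcomes of interest; Appendix 2): D − O
- Patient delay (Appendix 2): S − O
- Health system delay (Appendix 2): T − S
- Sum of the two named components: (S − O) + (T − S) = T − O, which is total delay
- Excess over diagnosis delay: (T − O) − (D − O) = T − D, which is treatment delay

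The two readings differ for each patient by exactly the treatment delay. The document gives no value for that interval, so the excess in days cannot be stated.

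**2. Cost window.**

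| Component | Measurements | Appendix 2, catastrophic cost |
|---|---|---|
| Direct medical | diagnosis and treatment | onset to end of treatment |
| Direct non-medical | before and during diagnosis | onset to end of treatment |
| Indirect | TB episode | onset to end of treatment |

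Only the second row conflicts. Let C be a household's cost under Measurements, N ≥ 0 its non-medical spending during treatment, and Y its annual income. Measurements classifies on C > 0.20Y, and Appendix 2 on C + N > 0.20Y. Because N ≥ 0, every household counted under Measurements is also counted under Appendix 2. Households with C ≤ 0.20Y < C + N are missed. The Measurements share is therefore never higher, and it is lower as soon as one household falls in that band. The document gives no cost distribution, so the size of the shortfall cannot be computed.

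**3. Which cost endpoint was powered.** Inputs from the cost sample-size section: P1 = 0.40, P2 = 0.27, alpha 0.05 (taken as two-sided), power 80%, 10% non-response. The pooled-variance formula without continuity correction is

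n per arm = [1.960·√(2·p̄·(1 − p̄)) + 0.842·√(P1(1 − P1) + P2(1 − P2))]² / (P1 − P2)², with p̄ = 0.335.

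- First term: 1.960 × √0.44555 = 1.308
- Second term: 0.842 × √0.4371 = 0.556
- n = (1.308 + 0.556)² / 0.0169 ≈ 205.8, so 206 per arm and 412 in total
- Adding 10%: 412 × 1.10 = 453.2, against 453 stated
- Stated total × 0.95: 453 × 0.95 = 430.35, against 428 stated (214 per arm)

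The stated 453 is reproduced, so the powered endpoint is the binary proportion. No mean, standard deviation or detectable difference in cost is given, so power for the change in cost cannot be derived. For scale only, and ignoring clustering, 214 per arm gives 80% power for a standardised mean difference of (1.960 + 0.842) × √(2/214) ≈ 0.27.

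**4. Follow-up for treatment-phase costs.** Assumptions not in the document: a 6-month course, uniform accrual over the window, and closure on 31 January 2024.

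- Randomization and recruitment dates: the last patient enters on 30 September 2022 and finishes around the end of March 2023, before closure. Incomplete share: 0%.
- Trial status dates: the window from 1 July 2022 to 30 December 2023 is 547 days. Entries after 31 July 2023 cannot finish by closure, and 31 July to 30 December 2023 is 152 days. Incomplete share: 152/547 ≈ 28%.

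**The case against.** The strongest reply is that these are wording slips in secondary outcomes and that the intended meaning is recoverable. Several parts of it stand.

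- A reader might infer that diagnosis delay has two competing end points. It does not. Outcomes of interest and Appendix 2 both stop it at diagnosis, and only the description of its components conflicts.
- A reader might infer that transport and food during treatment are left out for every patient. That holds only if Measurements overrides Outcomes of interest, which lists those items with no time limit, and Appendix 2.
- A reader might take 28% as the share of patients with truncated costs. It is the upper end of a range that starts at 0%, and it is a share of the recruitment window under three assumptions.
- A reader might infer bias between the arms from late recruitment. That needs the arms to recruit at different times, and nothing in the document indicates this.
- A reader might conclude that the powered cost question is never tested. The Abstract says in general terms that GLMMs will compare the outcome of interest between arms, and such a model can take a binary outcome. For delay, Data analysis does plan logistic regression, so the same complaint does not carry over.

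An analysis plan that is not shown could name the test. That does not remove the point, because Data analysis already ties the mixed model to change of cost and lists the outcomes for logistic regression without catastrophic cost. Nor can condensation for a journal explain definitions that are printed in full and disagree.

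**Conclusion.** The concern holds in three limited parts.

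1. The window for direct non-medical cost in Measurements contradicts the catastrophic-cost numerator in Appendix 2. Following Measurements understates the share above 20%. The direction is certain, but the size cannot be derived from the document.
2. The cost objective is sized on the catastrophic-cost proportion (40% versus 27%, reproduced to rounding at 453), but Data analysis names no comparison of that proportion.
3. Diagnosis delay ends at diagnosis, but the components said to make it up sum to total delay. The discrepancy equals each patient's treatment delay.

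The conflicting recruitment dates leave the share of the recruitment window with incomplete treatment-phase costs anywhere from 0% to about 28%, under the 6-month, uniform-accrual and 31 January 2024 assumptions. No between-arm bias is claimed. The primary outcome is not affected. The changes are worth making because the cost and delay calculations are the only ones that fix patient numbers (428 and 416).

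**What to change.** - **Cost window.** In Measurements, use symptom onset to end of treatment for every component, including transport, accommodation and food, and align the questionnaire. This costs wording, plus a later cost interview if one is not already planned.
- **Cost test.** In Data analysis, name a comparison of the catastrophic-cost proportion between arms that accounts for clustering, for example a binomial GLMM, as the tested cost endpoint. Keep the cost amount as supportive. This needs no extra data.
- **Delay.** Compute diagnosis delay directly as the diagnosis date minus the onset date, end its health-system part at diagnosis, and report total delay separately. This costs wording, and the treatment start date must be recorded.
- **Dates.** Reconcile the recruitment periods in Randomization and recruitment and in Trial status with the January 2024 closure, and state how costs to the end of treatment will be obtained for the last patients recruited.

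Restricting the cost analysis to early recruits is not recommended as a routine remedy. At the upper end of the range it would leave about 428 × 0.72 ≈ 308 patients (154 per arm). Power for 40% versus 27% would fall from about 82% to about 68%, ignoring clustering and non-response.
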